## Abstract

**Background:**

The alcohol-metabolizing enzyme aldehyde dehydrogenase 2 (*ALDH2*) is a carcinogenic acetaldehyde-degrading enzyme, and its low activity is a genetic constitution peculiar to East Asians. People with low alcohol dehydrogenase 1B activity (*ADH1B*1/*1* genotype) have a high risk of developing head and neck cancer and alcoholism. The study aims to evaluate the effectiveness of brief interventions for excessive drinking among college students and adults in their 20s, including information on five constitutions that combine the *ALDH2* and *ADH1B* genotypes.

**Methods:**

Participants comprised university students and staff aged 20–30 years who had consumed ≥40 g (males) or ≥20 g (females) of pure alcohol; they were classified into intervention and control groups using a simple randomization method. Participants anonymously filled out questionnaires linked to identification numbers and recorded the drinking days and amounts on the drinking calendar. The intervention group will then be tested for genotype testing using saliva (5 types of combinations of *ALDH2* and *ADH1B* enzyme activities); the result report will arrive approximately 1 month later. We will conduct a 30-min face-to-face or online intervention. The control group will be merely given the conventional materials, and genetic testing will be performed voluntarily after 6 months (end of study). The intervention group will undergo questionnaire surveys 1 month after the intervention and 3 and 6 months after baseline. Questionnaire surveys will be conducted 1, 3, and 6 months after baseline for the control group. The average amount of drinking before and after the intervention, attribute/baseline data between the two groups, and time-series data were compared using various analysis tools. For interventions, we engaged in dialog based on intervention materials that added genotyping content to the existing materials, result reports, baseline data, and drinking calendar records. Participants’ ingenuity is respected to support their drinking behavior and goal setting.

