### Measures

From the self-written questionnaire anonymized by an identification number, basic attributes (age, sex, main areas of learning, living with or without family, work situation, participation in circles, and hobby activities) and evaluation items will be investigated. For the intervention group, we will collect data 1 month after the intervention, and 3 and 6 months after the questionnaire survey at the time of consent procedure.

At the same time as the questionnaire survey, the content and amount of drinking will be recorded in a drinking calendar for half a year anonymized by the identification number. For the questionnaire and drinking calendar, the researchers (mainly the first author) will ask the participants to answer by e-mail, and the data from the returned attached file will be collected. We will ask for a response within a week from the survey point, and if there is no response, we will optionally request a response by reminder email within a month.

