Japan’s Ministry of Health, Labor, and Welfare has listed support technology in the “Standard Health Checkup and Health Guidance Program Definitive Edition” and calls for “indifference, interest, preparatory period, execution period, and maintenance period” as “the preparation stage for behavior change,” and “to support the stage to improve by changing the support method for each stage” (definitive edition p86, revised version p121, 2018 edition p3-2) [31]. The five stages are as follows: (1) indifference period, lack of intention to take action toward behavior change within 6 months; (2) period of interest, willingness to take action toward behavior change within 6 months; (3) preparation period, willingness to take action toward behavior change within 1 month; (4) implementation period, observance of a clear behavior change at less than 6 months only; (5) maintenance period, clear behavior change lasting for more than 6 months [28]. In this study, the survey was conducted at baseline and four points up to half a year.

The modified PHCS Japanese version [29], which has eight items (5-step Lickert scale), was created by Smith, Wallston, and Smith (1995) according to self-efficacy theory as a performance index involved in changes in health-related habits and behavior. Its reliability and validity were verified by Togari et al. [29]. In addition, while alcohol has a hypnotic effect, drinkers are easily awakened because of the decrease in the blood concentration of alcohol and diuretic action after falling asleep; in fact, the association between binge drinking and sleep problems was suggested in young adults in particular [32]. Therefore, the presence or absence of binge drinking (within 2 h, >5 drinks for males and >4 drinks for females) and sleep status (recognition of sleep time and sleep quality: 4-step of Likert scale, difficulty falling asleep, and wakefulness during sleep) in the past month were added to our questionnaire. In addition, fatigue conditions will be investigated using SFS-Y [21], considering that the burden on the liver by excessive drinking leads to fatigue. We will also investigate the effect on class attendance and assignment submission on a 5-step Likert scale. SFS-Y has 24 items (6 subscales: difficulty in intensive thinking, fatigue, decreased motivation, decreased vitality, drowsiness, body discomfort), and it has been proven to be reliable and valid [21].

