## Alcohol-metabolizing enzyme genotype testing and results report

Briefly, the intervention group will read the instructions for the alcohol-metabolizing enzyme test, sign the consent form, undergo saliva collection using a sponge swab from the test kit, and receive a report of the results approximately after 1 month. The inspection contractor will mail the result report to the participants. If face-to-face explanation and inspection are difficult to conduct, the test kit will be mailed to the participants.

In the control group, testing will be conducted on those who wish to be tested after 6 months from baseline. After receiving the test results, their requests will be confirmed, and the intervention will be performed.

Regarding the report of the results of the alcohol-metabolizing enzyme test, we have created a pamphlet that includes contents common to each of the five types of constitutions and the contents for each constitution. The main contents are as follows:Participants’ alcohol constitution (what type of constitution from A to E, characteristics by constitution type)Mechanism of alcohol decomposition, function of metabolic enzymes, and constitution by combinationRisks of diseases associated with drinking by alcohol constitution (every five types) and points to remember (comments by the constitution)How to interact with and drink alcohol that suits participants’ alcohol constitution, and how to absorb alcohol ingenuity in nutrition and eating and drinking to help slow down the metabolismDrinking habit screening test (AUDIT-C)Appropriate drinking and liver rest days, proper drinking method, alcohol calorie, and metabolism, obesity, etc.Inappropriate drinking: drinking while pregnant/lactating, drunk driving, alcohol harassment, and habitual use/heavy drinking

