### Actual intervention

Participants in both the intervention and control groups can lead a normal life, with no particular restrictions or changes in daily care, which will continue in both study groups.

Interventions will be conducted according to the results of individual test results, baseline questionnaire data, drinking calendar records, and health guidance materials, including conventional teaching materials [33]. The main contents of the health guidance materials are as follows:Alcohol action (disinhibition/relaxation, sedation/anesthesia, blood alcohol concentration, and drunken stages and symptoms)Mechanism of comfort and discomfort associated with drinking (relationship with neurotransmitters in the brain reward system, action of alcohol-metabolizing enzymes, harmfulness of acetaldehyde)Alcohol constitution (what type of constitution from A to E, characteristics, and comments by constitution type)Drinking habit screening test (AUDIT-C: ≥6 points for males, ≥4 points for females) and feedback that continuing the current drinking habits may eventually affect the mind and bodyDrinking amount ranking based on the current drinking amount (national standard table of drinking for general adult males and females)Generally appropriate amount of alcohol: two drinks for males (20 g of pure alcohol) or less on average per day, one drink (10 g of pure alcohol) or less for femalesThe number of people who are vulnerable to alcohol, who are older, and who have a red face when drinking alcohol is even lessGenerally inappropriate drinking (drinking while pregnant/lactating, driving a car (including a bicycle), minor, illnesses, or medications affected by drinking)Drinking with a high risk for lifestyle-related diseases: four drinks for males on average per day (40 g of pure alcohol) or above, two drinks for females (20 g of pure alcohol) or aboveBinge drinking: within 2 h, five drinks for males (50 g of pure alcohol) or more, four drinks for females (40 g of pure alcohol) or moreInformation from recent studies: zero daily drinking may be desirableParticipants’ intentions regarding drinking behavior and drinking habits (continuing or reviewing the current drinking habits is better)Participants’ opinion about the advantages and disadvantages of drinking alcoholReview on how to drink, the possible goal, and the concrete methodExamples of self-monitoring: proposal for continuing the drinking diary and drinking calendar recording

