As mentioned in the introduction, a randomized controlled trial using the genetic information of the alcohol-metabolizing enzyme *ALDH2* validated the effect 30 days after providing Internet-based *ALDH2* genotype and health risk information [13]. In this previous study, the frequency and amount of drinking were significantly reduced after 30 days in the feedback group with low *ALDH2* activity. However, their follow-up period was 30 days, which is shorter than 6 months (maintenance period) [28], for behavioral habituation and maintenance. Therefore, the strength of the current study is the investigation of the intervention effect until 6 months (maintenance period) [28], which is the standard duration for behavioral habituation, and verification of its long-term efficacy.

Conversely, one limitation of this study is that when students agree to participate, they already know if they are in the group to be tested or not; hence, they cannot be blinded. Regarding the primary outcome measure, the average drinking amount on the drinking day is limited to the calculation of the amount of drink with an unknown alcohol concentration or amount. In addition, given that this research deals with genetic information, we need to evaluate the intervention effect by interviewing each participant. We also need to examine a system that can be useful for enrolling large groups, such as university students.

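### The first follow-up survey runs on a different clock in each arm, and the six-month maintenance claim outruns the follow-up after the session

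*Protocol article*

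**What the plan says.** The Abstract (Methods) gives the arms different survey schedules. For the intervention arm: "The intervention group will undergo questionnaire surveys 1 month after the intervention and 3 and 6 months after baseline". For controls: "Questionnaire surveys will be conducted 1, 3, and 6 months after baseline for the control group". The Measures section repeats the intervention arm's mixed clock: "we will collect data 1 month after the intervention, and 3 and 6 months after the questionnaire survey at the time of consent procedure". So this is not a slip confined to the Abstract.

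The session cannot take place at baseline. The Abstract says of the genotype test that "the result report will arrive approximately 1 month later", and the section on genotype testing says participants "receive a report of the results approximately after 1 month". The section on the actual intervention makes the session depend on that result: "Interventions will be conducted according to the results of individual test results, baseline questionnaire data, drinking calendar records". Controls receive their handbook during the consent procedure.

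On durability, the Secondary outcome measures section defines the fifth stage of change as "maintenance period, clear behavior change lasting for more than 6 months". The Discussion states that "the strength of the current study is the investigation of the intervention effect until 6 months (maintenance period"), and presents this as verifying long-term efficacy.

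**The concern.** Randomisation makes the arms comparable at a common time since enrolment. At the first follow-up there is no common time. The questionnaire asks about average drinking over the preceding month, so the two arms describe different months after enrolment. They have also kept the drinking calendar for different lengths of time, and self-monitoring may itself change drinking. A difference at this survey could not be attributed to the genotype-based session alone.

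The comparison is open to being made. The Abstract says time-series data are compared. The Statistical analysis section compares the arms on change in drinking before and after the intervention, and does not confine this to the surveys that are aligned. The first follow-up is a natural choice for the after-intervention value.

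The second issue is what can be claimed at the end. If the last survey is less than 6 months after the session, a change begun at the session cannot meet the protocol's own definition of maintenance within follow-up.

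**Working it through.** **Inputs**

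- Intervention arm, first survey: 1 month after the session (Abstract; Measures).
- Control arm, first survey: 1 month after baseline (Abstract).
- Later surveys, both arms: 3 and 6 months after baseline (Abstract; Measures for the intervention arm).
- Delay from test to report: about 1 month (Abstract; genotype testing section).
- Delay from report to session: not stated. Assumed 0 to 1 month.
- Recall period: the past month (Primary outcome measures).
- Maintenance: more than 6 months (Secondary outcome measures).

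**Formulas.** Let T be the session time in months from baseline, T = report delay + scheduling delay.

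- Intervention first survey = T + 1; control first survey = 1; gap = (T + 1) − 1 = T.
- Recall window at the first survey: T to T + 1 (intervention), 0 to 1 (control).
- Time from session to a later survey: 3 − T and 6 − T.

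**The protocol's own figure.** Counted from baseline, the last survey is at 6 − 0 = 6 months, so the 6 months in the Discussion reproduces on that clock only. Counted from the session it is 6 − T.

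**Results**

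| T (months) | First survey, intervention / control | Gap | Recall window, intervention / control | 3-month survey, months after session | 6-month survey, months after session |
|---|---|---|---|---|---|
| 1.0 | 2.0 / 1.0 | 1.0 | 1.0–2.0 / 0–1 | 2.0 | 5.0 |
| 1.5 | 2.5 / 1.0 | 1.5 | 1.5–2.5 / 0–1 | 1.5 | 4.5 |
| 2.0 | 3.0 / 1.0 | 2.0 | 2.0–3.0 / 0–1 | 1.0 | 4.0 |

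At T = 1 the nominal recall windows do not overlap, and calendar-keeping has lasted about 2 months in one arm and 1 in the other. At T = 2 the intervention arm's first survey coincides with its own 3-month survey.

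If the report came early, at T = 0.75, the first survey would be at 1.75 months, the windows would overlap by 0.25 month, and the last survey would be 5.25 months after the session. That is still under 6.

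**Maintenance.** Observing more than 6 months after the session needs a last survey later than 6 + T: after month 7 if T = 1, after month 8 if T = 2. Even counted from baseline, 6 is not more than 6.

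**Would one month after baseline in both arms solve it?** No. At T = 1 that survey falls at about the time of the report or session and would measure no effect of it.

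**The case against.** The strongest defence is that each arm is surveyed one month after its own exposure: controls after the handbook at consent, the intervention arm after the session. That is a coherent reason for the schedule, and a survey one month after baseline would indeed be uninformative in the intervention arm. But it aligns time since exposure only. Time since enrolment, the month recalled and the length of self-monitoring still differ.

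Three further points limit the concern, and they stand.

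- A reader might infer that the trial's between-arm comparisons are biased in general. They are not: the 3- and 6-month surveys are timed from baseline in both arms. Nor does the article say that the first survey carries the main conclusion.
- A reader might infer serious confounding by season or COVID-19 measures. Recruitment is rolling, from July 2021 to March 2023, with random allocation, so a shift of a month or two is spread over about 20 months of enrolment and such effects largely average out. Time since enrolment does not average out.
- A reader might infer that the stage-of-change outcome cannot be delivered. The protocol specifies no endpoint of reaching maintenance, and the Discussion's stated hope is a move from indifference to interest, which is observable within follow-up. Follow-up of about 5 months after the session also remains far longer than the 30 days of the earlier internet-based trial with which the Discussion compares itself.

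The absence of overlap in recall is also nominal. The report delay is approximate, and late replies can be accepted after a reminder for up to a month, so some individual windows will overlap.

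**Conclusion.** The concern holds in a limited form. The first follow-up surveys are misaligned by about 1 month, or up to 2 if scheduling the session adds a month, and should not be compared between arms. The 3- and 6-month contrasts are sound with respect to time since baseline. The direction and size of any resulting bias cannot be worked out from the document.

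The description of 6-month follow-up as the maintenance period conflicts with the protocol's own definition and with its timetable, which gives about 5 months after the session at most (4 to 5 for T between 1 and 2). An effect at 6 months after baseline can still be estimated; what the schedule does not support is calling it maintenance of change begun at the session.

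These figures rest on the stated report delay of about a month and on the assumed scheduling delay of 0 to 1 month.

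**What to change.** 1. Base between-arm inference on the surveys at 3 and 6 months after baseline. Report the first follow-up survey within each arm only.
2. For a short-term contrast, use the planned half-year drinking calendars over identical days from baseline in both arms, covering the first month after the session: for example about days 31–60, or a slightly later common window if sessions are delayed. Fix the window for everyone before the data are examined; do not set it by each participant's session date. Days 61–90 would add little, because the 3-month questionnaire already recalls that month in both arms.
3. Reword the Discussion to say that the effect is followed to 6 months after baseline, about 5 months after the session, and do not interpret stage-of-change results as maintenance attributable to the session.

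The cost is small: wording, and some extra analysis of data already planned for collection. No additional surveys or participants are needed. The durability claim becomes slightly weaker. Where a session is late, a common calendar window will include some days before it, which dilutes the short-term contrast but keeps the randomised comparison intact.

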**Discussion:**

Individual information on the genetic makeup of alcohol-metabolizing enzymes provided during the intervention is more personal and objective than general health information, especially in Japan, where the *ALDH2* low activity rate is high. This information may be useful for health care and precautionary measures.

**Trial registration:**

R000050379, UMIN000044148, Registered on June 1, 2021.

Scientific Title: Examination of simple intervention using genetic polymorphism information for excessive drinking.

## Background

A genetic constitution with a low *aldehyde dehydrogenase 2* (*ALDH2*) activity is atypical in East Asians [1]. In Japan, less than 10% of the population is *ALDH2* homodeficient, whereas 30–40% is *ALDH2* heterodeficient [2]. In Japan, Taiwan, and China, *ALDH2* heterodeficient drinkers have a particularly high risk for esophageal and head and neck cancer, and *ALDH2* heterozygous deficiency is strongly associated with multiple carcinogenesis and juvenile carcinogenesis [2]. The results of all Japanese and Chinese case–control studies on the association between esophageal cancer and *ALDH2* heterozygotes deficiency showed that *ALDH2* heterozygous deficiency increased the risk of esophageal cancer in drinkers (5.3–16.4 times the adjusted odds ratio). This tendency is not limited to heavy drinkers, and recent studies have shown a similar tendency in women [3]. *ALDH2 * 2* allelic carriers with low *ALDH2* activity were reported to have more than 10-fold higher blood acetaldehyde levels after alcohol intake than wild-type homozygotes (** 1 / * 1*) [4].

In the USA, alcohol consumption among young adults aged 18–44 years is a risk factor for cancer development, indicating that alcohol screening and intervention in this age group are crucial [5]. Additionally, the relationship between gene polymorphisms in alcohol-metabolizing enzymes and the risk of alcohol-related health problems includes the risk of developing acute alcohol intoxication with inactive *ALDH2*. *Alcohol dehydrogenase 1B* carriers (*ADH1B * 1 / * 1* genotype) have been reported to be at increased risk of alcohol dependence [2], as well as an increased risk of head and neck cancer due to excessive alcohol consumption [6–8]. Specifically, *ADH* gene polymorphisms also affect alcohol consumption, with *ADH1B * 1 / * 1* having slower ethanol metabolism than ** 2* allelic carriers and long-lasting drunkenness [4]. The combination of *ADH1B * 1 / * 1* and *ALDH2 * 1 / * 1*, which is common in Caucasians, tends to increase alcohol consumption. Higuchi et al. reported that the risk of alcoholism was approximately 6–10 times higher [9]. However, the combination of *ADH1B * 1 / * 1* and *ALDH2 * 1 / * 2* also has a high risk of alcoholism. Of the 26% people who drank ≥60 g of pure alcohol per day [10], 13% had alcoholism [9] and *ALDH2 * 1 / * 2*. Looking at *ADH1B * 1 / * 1* alone, the risk of esophageal cancer in drinkers was 2.71–3.22 times higher; however, the combination of *ADH1B * 1 / * 1* and *ALDH2 * 1 / * 2* had 12.45 times higher risk [11]. In any case, excessive drinking is harmful to the physical and mental health. In particular, *ALDH2 * 2* allele carriers are considered more harmful due to the accumulation of acetaldehyde [4]. Therefore, it is important to understand the genotypes of alcohol-metabolizing enzymes and make brief interventions for each genotype in terms of preventing cancer, addiction, and acute alcohol intoxication.

On the contrary, a systematic meta-analysis review in 2016 examined the effect of communicating genetic risk of disease on the risk-reducing health behaviors based on the results of multiple literatures [12]. The overall conclusion of the meta-analytic review stated that the expectation that transmission of DNA-based risk estimates would alter behavior was not supported by existing evidence [12]. In this review, the use of alcohol was examined based on three studies [13–15]. Those three studies assessed self-reported alcohol use, with genetic risks communicated for cancers [13, 15] and cardiovascular diseases [14]. Comparisons were between DNA-based risk estimates versus no risk estimates. Pooled data (*n* = 239) revealed no evidence of an effect of DNA-based risk communication on reducing alcohol use [12].

However, each of those studies examined alcohol use, and a 2010 American evaluation study [13] used the Internet to examine the genotype and health risk feedback effects on *ALDH2*. Results showed that the frequency and amount of drinking after 30 days were significantly reduced in participants with low *ALDH2* activity who received genetic feedback, which they highly appreciated [13]. This study population was composed of 200 college students (males, 46.5%; mean age, 20.2 years [SD = 1.5]), and they were assigned randomly to a group with genetic feedback (*n* = 100) or a group with attention without genetic information. The *ALDH2* genotype was analyzed using blood samples [13]. In addition, in a 2006 report [15], 329 male employees who wanted to know the results of the ALDH2 genotype were randomly divided into two groups. One is the “notified group” (*n* = 157), and the other is the “unnotified group” (*n* = 172). Patients in the “notification group” were notified of the results of the *ALDH2* genotype diagnosis, and drinking habit and liver function test data were obtained before and after notification of the *ALDH2* genotype. As a result, no significant change was found in the drinking frequency, and liver function test data did not decrease in any group before and after genotype notification. However, in patients with *ALDH2* activity genotype *ALDH2 * 1 / * 1*, weekly drinking tended to increase than that before notification, and *ALDH2* low-activity genotype *ALDH2 * 1 / * 2* patients tended to increase in the unnotified group, but decreased in the notified group. No significant differences were noted in the results, but further studies and increased sample size suggested that genetic testing might be useful [15]. In addition, Hanna-Leena et al. [14] reported a long-term follow-up study in 2018 on the disclosure of personal genetic risk information (APOE: apolipoprotein E) for cardiovascular diseases to promote a healthy lifestyle in Finland [16]. In conclusion, receiving information on increased personal genetic risk (carrier status of APOE ε4) for cardiovascular diseases provided the motivation for improvements in health behavior. The resulting changes, while modest, in most cases remained visible even after a few years [16].

A recent Korean research [17] introduces a previous study by Japan [18]; after drinking the same amount of alcohol, *ALDH2 * 2* homozygotes and heterozygotes showed 18- and 5-fold higher blood alcohol levels than *ALDH2 * 1* homozygotes, respectively, suggesting that interventions in alcohol use should be specified individually for each genotype. The paper emphasizes the role of *ALDH2* polymorphisms in alcohol-related health problems, requires consideration of *ALDH2* genotypes in alcohol prevention programs, incorporates genetic information, and informs people about alcohol consumption. They suggested an urgent need for a strategy that would provide the basis for evidence to support evidence-based decision making [17].

In 2009, Ishikawa et al. reported the intervention effect of correcting the drinking behavior problem in Japan by using the gene polymorphism information of alcohol metabolism [19], and they provided health guidance by adding the gene polymorphism information of *ALDH2*. They discovered that the average daily drinking after 6 months was significantly lower in the intervention group than in the control group without genetic information and that the ratio of drinking behavior patterns classified by drinking amount and frequency was significantly improved [19]. They also classified *ALDH2* into three types: (1) normal type homo (*ALDH2 * 1 /ALDH2 * 1* type); (2) normal type and mutant type hetero (*ALDH2*); and (3) ** 1 /ALDH2 * 2* type, variant homo (*ALDH2 * 2 /ALDH2 * 2* type). The first two were used for male adults in Japanese offices during blood sampling tests. Ishikawa, who is also an industrial physician at the business establishment, provided individual health guidance [19]. The intervention effect was based on the previous questionnaire on drinking habits and was compared with the results on drinking habits using the same questionnaire 6 months later. In 2017, Taketani et al. investigated 32 university students and graduate students aged 20 to 29 at one university as young adults in Japan. They examined the difference in alcohol education usefulness between the group that was notified of the genotype of enzymes (*ADH1B*, *ALDH2*) and the group that was not notified (hereinafter referred to as the “non-notification group”) by comparing the results of the questionnaire designed for their study [20]. They found that the amount of change in the knowledge of alcohol-related problems after alcohol abuse education was not significantly different between the two groups. However, presenting a scientific constitution using genotypes may improve their drinking behavior, including reconsidering their future drinking behavior [20].

One of the effective intervention methods presented by the National Institute on Alcohol Abuse and Alcoholism for overdrinking among college students is a simple method known as Brief Alcohol Screening and Intervention for College Students (BASICS). BASICS includes initial screening to identify high-risk drinkers, subsequent baseline assessments to generate individualized feedback, and one-on-one meetings with trained facilitators to confirm feedback [21]. According to a 2020 report of a randomized clinical trial conducted in India by Kumar et al. [22], out of 793 students from two universities screened using the Alcohol Use Disorder Identification Test (AUDIT), 130 had an AUDIT score of 8–19. These 130 participants were randomly assigned to two groups: an experimental group (*n* = 64) with individually tailored brief intervention by trained nurses and a control group (*n* = 66), which only received general advice. Intervention effectiveness was assessed 3 months after one session of screening and brief intervention (SBI) and compared in terms of the changes in the AUDIT score and the percentage of students transitioning from the high-risk zone to the low-risk zone between the two groups. According to the results, SBI provided by individual-based nurses reduced the severity of problems or hazardous drinking in the short term (after 3 months of intervention), but the estimated effect size was small (0.16) [22]. In addition, face-to-face individual interventions are costly and difficult to disseminate on a large scale; thus, the effectiveness of individual short-term alcohol interventions provided by computers for heavy-drinking college students and young adults has also been tested. In a 2015 US review, the effects of computer delivery interventions were positive but small [23].

Integrating the results of previous studies above, interventions for excessive drinking in college students and young adults will be more effective and enduring with individual brief interventions using gene polymorphism information for alcohol metabolism than previous brief interventions. Moreover, this intervention may enhance the effect of correcting excessive drinking, especially in Japan, where *ALDH2* is often inactive. This randomized controlled trial aims to clarify that.

This study examines individual brief intervention methods, including information about *ALDH2* and *ADH1B* genotypes (5 types) for excessive drinking among university students and staff aged 20–30 years as young adults. The study is currently recruiting participants, collecting data, and conducting some analysis. To verify the effectiveness of this intervention, this paper reports the study protocol.

